#### Aim 1: Determine provider and patient receptivity, barriers, and facilitators to implementing the nurse-administered, inpatient Tobacco Tactics intervention versus usual care using face-to-face feedback and surveys

Descriptive statistics (means and frequency distributions) will be used to summarize the nurses’ survey results. Patient participation rates will be calculated by dividing the number of inpatient smokers that participated by all smokers screened and found to be eligible to participate. Descriptive statistics will be calculated to determine if smokers were offered specific cessation services, whether they participated in these services, and their satisfaction with these services. Satisfaction rates of 80% are anticipated because our similar in-clinic smoking cessation intervention with head and neck cancer patients had similar rates [4]. To test for differences between the Tobacco Tactics and usual care sites in services received (yes/no) and satisfaction with those services (scale of one to five), GEE analysis using a link function of logit (for dichotomous dependent measures) or identity (for quantitative dependent measures) with adjustment for the clustering of patients within units will be conducted. GEE analysis is designed for data that are collected in clusters (the hospital units) and works with data with a wide variety of distributions.

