### Setting and sample

The setting will be six of forty-seven hospitals in the Trinity healthcare system, which is the fourth largest Catholic health-care system in the United States with facilities in nine states. All units will be included, including general medical/surgical, intensive care units/critical care units (ICU/CCU), psychiatric mental health, obstetrics and gynecology (OB/GYN), and pediatrics. The rationale for including all units results from our VA experience where we found exclusion of specific units to be unsuccessful, as specialty units initially excluded (for example, psychiatric mental health and ICU/CCU) felt discriminated against and felt they needed the intervention at least as much as the other units. Moreover, JC standards do not exempt specialty units therefore inclusion of all units is consistent with real world standards. That said, we recognize the need for adaptation of the intervention to specific units such as OB/GYN or pediatrics where the medication component may not be applicable, but the behavioral component would still apply. Including as many units as possible will increase the generalizability of study findings.

Inclusion criteria for the study include inpatients that: 1) are at least 18 years of age; 2) have smoked a cigarette within one month prior to hospitalization; 3) have a projected hospital stay of at least 24 hours; and 4) are willing to complete the questionnaires. The study will exclude inpatients that: 1) refuse to participate; 2) are involved in a concurrent trial that includes a smoking cessation intervention; 3) are non-English speaking (the intervention is currently only in English); 4) are unavailable to participate (for example, never in the room when the research assistant attempts to consent); 5) are not cognitively able to participate; or 6) are not physically able to participate (see Table 2).

**Table 2 T2:** Eligibility criteria

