**Inclusion criteria**	
1. at least 18 years of age	
2. smoked a cigarette within one month prior to hospitalization	
3. projected hospital stay of at least 24 hours	
4. willing to complete the questionnaires	

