**Exclusion criteria**	
1. refuse to participate	
2. involved in a concurrent trial that includes intervention on smoking	
3. non-English speaking (the intervention is currently only in English)	
4. unavailable to participate	
5. not cognitively able to participate	
6. not physically able to participate	

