### Power analysis

The six Trinity sites for the study (three intervention and three control) employ 3,553 inpatient nurses that work across fifty-eight units and discharge 98,350 patients per year (see Table 3). Of the 98,350 annual patients served by the Trinity hospitals, we conservatively estimate that 80% (78,680) of the inpatients will be well enough to participate and, of these, 20% (15,736) will smoke. Based on our previous studies, we anticipate that 50% will agree to participate for a potential recruitment pool of 7,868, which will be more than enough to recruit the 2,350 smokers needed for 80% power to detect a significant difference in cessation rate (the primary outcome) assuming a 30% cessation rate in the intervention group versus 20% in the usual care group, with an alpha of .05. This power analysis was based on the patient as the unit of analysis with attention to clustering by hospital unit. Effects of the clustering on the power of the study were based on intraclass correlation coefficients (ICC) from our preliminary study and the number of clusters in the design. Using the hospital unit as the unit of clustering was justified given that the study is quasi-experimental rather than experimental and that any other analysis would be underpowered.

**Table 3 T3:** Description of six hospital sites

**Group 1**	**RN positions**	**Number of units**	**Annual discharges**	**% minorities**	**Group 2**	**RN positions**	**Number of units**	**Annual discharges**	**% minorities**
Hospital 1	659	11	19,800	70%	Hospital 4	502	12	18,250	31%
Hospital 2	326	9	17,000	4%	Hospital 5	536	8	20,500	29%
Hospital 3	765	9	11,400	27%	Hospital 6	765	9	11,400	48%
**Total**	**1,750**	**29**	**48,200**	**17,618/48,200 = 37%**	**Total**	**1,803**	**29**	**50,150**	**17,075/50,150 = 34%**

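### The Aim 1 patient participation rate, as written, leaves decliners and unreached smokers out of its denominator, so it reads about 100% whatever the true agreement

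*Protocol article*

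**What the plan says.** Four parts of the protocol article bear on this.

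- **Data analysis, Aim 1.** The patient participation rate is obtained by "dividing the number of inpatient smokers that participated by all smokers screened and found to be eligible to participate".
- **Setting and sample.** Inclusion criterion 4 admits patients who "are willing to complete the questionnaires". On the other side, "The study will exclude inpatients that: 1) refuse to participate", and exclusion 4 removes those who "are unavailable to participate (for example, never in the room when the research assistant attempts to consent").
- **Table 2 (Eligibility criteria).** The same three conditions are repeated: "4. willing to complete the questionnaires" among the inclusions, "1. refuse to participate" and "4. unavailable to participate" among the exclusions.
- **Power analysis.** After restricting to inpatients well enough to take part and then to smokers, "we anticipate that 50% will agree to participate".

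The Overview under Procedures explains that taking part in the study means filling in its surveys. It adds that smokers who turn the research down are still offered the intervention in the intervention hospitals.

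**The concern.** A participation rate is informative only if those who could have taken part but did not are counted in its denominator. Here the eligibility list turns not taking part into a reason for being ineligible. A smoker who declines fails an inclusion criterion and meets an exclusion criterion; a smoker who is never reached meets an exclusion criterion. Neither is then available to be counted as an eligible non-participant.

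At stake is the meaning of one reported descriptive figure. Readers would take a rate near 100% as evidence that almost every eligible inpatient smoker enrolled, although the authors themselves plan on half agreeing. There is also a practical risk: staff who follow Table 2 would code refusers as ineligible, while staff who follow the order of steps in the Power analysis section would code them as eligible but not enrolled. Rates from hospitals that coded differently would not be comparable.

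**Working it through.** **Step 1. Reproduce the plan's own figure (Power analysis).**

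- Annual discharges: 98,350
- Well enough to participate: 98,350 × 0.80 = 78,680
- Smokers among them: 78,680 × 0.20 = 15,736
- Agreeing: 15,736 × 0.50 = 7,868

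The stated recruitment pool of 7,868 reproduces exactly. Agreement is treated here as a step that comes after a smoker has been counted as a candidate.

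**Step 2. Write the rate as defined.** Let S be the screened smokers who meet every criterion other than willingness, refusal and unavailability. Let R be those who refuse or are unwilling, U those who are unavailable, and P the participants.

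- Eligible under Table 2 = S − R − U
- P ≈ S − R − U, the only gap being smokers who say they are willing and then do not complete the baseline survey
- Rate as written = P / (S − R − U) ≈ 100%
- Rate with non-participants kept in = P / S

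**Step 3. Put the planning figures in.** Take S = 15,736 and P = 7,868 as an approximation.

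- As written: 7,868 / 7,868 = 100%
- Non-participants kept in: 7,868 / 15,736 = 50%

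**Step 4. Check whether the rate responds to what it names.**

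| Assumed true agreement | Rate as written | Rate with non-participants kept in |
|---|---|---|
| 30% | about 100% | 30% |
| 50% | about 100% | 50% |
| 70% | about 100% | 70% |
| 90% | about 100% | 90% |

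The written rate does not move with agreement.

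**Step 5. See what unavailability does on its own.** The document gives no share of smokers who are unavailable, so 5%, 10% and 20% of S are assumed here. Suppose P / S = 50% and only the refusers are restored, with the unavailable still left out. The rate is then 0.50 / (1 − u):

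- u = 5%: 52.6%
- u = 10%: 55.6%
- u = 20%: 62.5%

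So the handling of unavailable patients also changes the result, though less than the handling of refusers. This is why the two groups should be counted separately.

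**Limit of the 50% comparison.** The 15,736 base reflects only being well enough and smoking. It does not apply the projected-stay, language or concurrent-trial criteria. The 50% shows that the passages conflict; it does not predict the corrected rate.

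**The case against.** The strongest reply is that the authors plainly meant eligible before consent. The Aim 1 sentence itself separates screening from participating, the Power analysis section places agreement after candidacy, the Overview has all smokers offered participation, and the enrolment section has smokers identified from the nursing assessment and only then approached for consent. The recruitment flow chart (Figure 1) is not visible here and may show that order.

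This stands as evidence of intent. It does not settle the text: no visible passage defines eligibility for this rate apart from refusal, and the eligibility list says the opposite both in the prose and in Table 2. Nor is this a detail left to a fuller document, because the article states both the formula and the criteria, and they conflict.

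A reader might go further and infer two stronger things.

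- **That Aim 1 can no longer show reach or receptivity.** The document does not support this. The rate concerns survey participation, and smokers who decline the research are still offered the intervention, so even a corrected rate would not measure reach of the intervention. Receptivity and uptake are also captured by services offered and received, satisfaction, follow-up calls made and use of the manuals. Table 4 lists face-to-face feedback and surveys as the Aim 1 outcomes.
- **That the formula hides the main check for differential selection between conditions and periods.** No section gives the rate that role. Table 4 also shows an eligibility criteria log; if refusal and unavailability are recorded there as reasons, the counts can be recovered by hospital and period.

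**Conclusion.** The inconsistency is real. Applied literally, the Aim 1 formula returns about 100% at any true level of agreement, while the same document plans on 50%. It is about 100% rather than exactly so because a willing patient may still not complete the baseline survey.

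The consequence is limited to one untested descriptive measure of study participation. The six-month quit outcome, the sample size, and the services-received and satisfaction analyses do not depend on it. The conclusion rests on reading eligibility as Setting and sample and Table 2 define it. If the analysts in practice use a pre-consent definition, the computed rate will be sensible and only the wording is at fault. Either way the text should be corrected, because two people following it could report very different figures.

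**What to change.** In the Aim 1 analysis text, define the denominator as all screened smokers who meet every eligibility criterion other than willingness, refusal and unavailability. Count refusers (including the unwilling) and unavailable patients as non-participants, and report the two groups separately. Preferably give the rate by condition and by period from the eligibility log.

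Table 2 need not be rewritten, and who is enrolled does not change. The cost is one clause of wording and a check that the log records refusal and unavailability as distinct reasons. At the stated recruitment of 651 of 2,350, a clarification would still cover the remaining 2,350 − 651 = 1,699 enrolments. For smokers already screened, it works only if those reasons were logged, which the article does not say. The downside is presentational: the reported rate will be well below 100%.

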#### Aim 2: Compare the effectiveness of the nurse-administered, inpatient Tobacco Tactics intervention versus usual care across hospitals, units, and patient characteristics using thirty-day point prevalence abstinence at thirty days and six months (primary outcome) post-recruitment

Patients will report on their smoking status (thirty-day point prevalence) at thirty days and six months (primary outcome variable) post-recruitment. At six months, all study participants will be asked to return the completed cotinine test. Descriptive statistics (percentage quit for seven and/or thirty days at six months) will be computed and reported for the hospitals and units in each condition. The standard errors will be computed taking into account the clustering of patients within units. GEE analyses analogous to logistic regression, but adjusting for the clustering of patients within units, will be used to compare the pre- and post-intervention quit rates in the intervention as compared to the usual care control hospitals. Recall that in every hospital, quit rates will be assessed both before and after implementation of the intervention (whether or not the hospital is among those receiving the intervention). Whether the baseline quit rates differ or not between hospitals, baseline quit rates will be considered in analyses to meet this objective.

Smoking quit rates will be assessed throughout the implementation phase to assess whether cessation rates are improving; however, the primary outcome is the smoking cessation rates at the time when the intervention is independently being conducted by hospital staff. Descriptive statistics will be computed and reported. Preliminary analyses will use chi-square tests of association to compare the quit rates in the hospitals in each condition.

We anticipate a quit rate of 30% in the hospitals receiving the Tobacco Tactics intervention and 20% in the usual care hospitals. However, to assure that these differences are not just due to differences between the hospitals, a GEE analysis will be conducted using the logit link function with the hospital unit as the definition of the cluster analogous to moderated logistic regression analysis in which quitting is predicted by time frame (baseline versus intervention period), intervention group (Tobacco Tactics versus usual care), and the product of those two variables. The statistical significance of the product will indicate that the difference between the Tobacco Tactics and the usual care comparison sites depends on whether or not the intervention has been implemented. We anticipate no difference between the sites at baseline, but a notable difference after the interventions have been implemented.

In addition, harm reduction will be compared between the two groups by analyses of number of cigarettes smoked per day, number of quit attempts, and nicotine dependence (as indicated by Fagerstrom test). For each of these analyses, the same general approach taken to the primary dependent variable will be applied including: descriptive statistics on baseline and intervention period and a GEE with the hospital unit as the definition of the cluster analogous to moderated regression analysis to compare the differences between the sites (Tobacco Tactics versus usual care) by time (baseline versus intervention period). Both the descriptive statistics and the significance tests differ for these other outcome measures because of their different distributions (that is, normal or not). Count variables will be analyzed assuming a Poisson distribution using a log link function while the Fagerstrom test scores will be modeled with an identity link function since it is normally distributed.

Other analyses related to aim 2 will test the moderation of the effects of the interventions by selected patient characteristics. We hypothesize that patients will be more likely to quit if they have higher confidence in ability to quit, higher education level, lower addiction, lower alcohol intake, and a smoking-related diagnosis such as heart disease. We will also test whether the effects of the specific intervention (Tobacco Tactics or usual care) received are moderated by these factors. All of these effects will all be tested by GEE analyses analogous to moderated regression analyses (whether logistic, linear, or Poisson) including product terms to test the interaction of these factors with the intervention received.

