## Methods/Design

### Design

Since many randomized controlled trials have already tested the efficacy of inpatient smoking cessation interventions [1], the real challenge is integrating these interventions into standard of care. Hence, this effectiveness study will use a quasi-experimental design in six Michigan community hospitals of which three will get the nurse-administered Tobacco Tactics intervention and the other three will provide usual care in accordance to how the hospital responds to current Joint Commission (JC) hospital accreditation standards. Implementing the intervention at the facility (hospital) level was the most likely design to remain sustainable once the study was completed.

Throughout the entire study, smokers are surveyed at baseline, thirty days and six months post-recruitment. In this way, quit rates at two time points for all patients are determined during intervention (of less interest), and post-intervention in both the Tobacco Tactics and usual care groups. There are two sources of control. The first source of control is pre- versus post-intervention changes within hospitals; this source of control will NOT control for seasonal changes. The second source of control is changes in the Tobacco Tactics sites compared to the usual care sites; this source of control WILL control for seasonal changes and any other historical events that may influence quit rates across sites.

The quasi-experimental design allows for implementation in natural environments minimizing threats to external validity as natural environments do not suffer the same problems of artificiality as compared to a well-controlled laboratory setting [7]. While quasi-experimental designs are more feasible, the lack of randomization at the patient level may pose many challenges in terms of internal validity making it hard to rule out confounding variables [8]. To minimize the effect of confounding variables, the six hospitals have been split into two groups of three that as a group are matched on hospital size and percentage of minority patients. While we could have arbitrarily decided which group of three hospitals gets the intervention and which does not, we wanted to reduce investigator bias and used a computerized coin flip to assign the groups to experimental and control conditions. See Table 1 for the overall study design.

**Table 1 T1:** Overall study design

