**Socio-demographics**					
· Demographics (age, sex, race, educational level, marital status, employment, hospital site)*	**X**	**X**	**X**		

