### Data analysis

All analyses that compare the two treatment groups will use the intent-to-treat approach in which patients’ data are analyzed based on the treatment intended, not on the treatment actually received. This approach is taken because it is the best method for evaluating the potential effects of disseminating the Tobacco Tactics intervention, which is our focus. Another implication of this approach is that the approximately 25% of patients who are lost to follow-up are included which assures that differences between conditions are not actually due to differential drop out. Extensive follow-up will be conducted including by telephone to minimize the amount of missing data. Statistically justified imputation methods such as multiple imputation will be used to allow analyses including those who have dropped out.

Analyses will adjust for clustering for patients within units using generalized estimating equations (GEE) analyses. GEE is a method of analysis that can account for the correlations among responses from patients in the same cluster [31]. Given the structure of the study with patients nested within hospital units, the hospital unit will be treated as the cluster. The correlation matrix will be of the exchangeable form, assuming the same correlation among any pair of patients in the same hospital unit. This is standard structuring of the matrix for analyzing clustered non-longitudinal data. Given concerns that GEE might be biased with a small number of units, the adjustment for that factor recommended by Morel [32] will be used for each GEE analysis.

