There is concern that individual hospitals might differ in factors that influence implementation and effectiveness of the intervention. Though the study would be underpowered to use the hospital as the unit of clustering, several strategies will be used to counter the effects of hospital differences on our finding. If there are baseline differences in the type of patients among the six hospitals, we can control for these differences by adding these variables as covariates in the analysis. If there are multiple differences and we are underpowered to add all of these variables as covariates, we will create a propensity score to control for these differences. Note the quit rates and other factors will be assessed in all hospitals before the intervention is conducted in any of them. Comparison of the post-intervention quit rates to the pre-intervention quit rates (and post and pre levels of other outcomes) is built into the analyses.

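### The deciding Aim 2 model has no hospital term, so an unmatched shift in hospital mix between periods can bias the period-by-group product

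*Protocol article*

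**What the plan says.** Under Aim 2 in Data analysis, the Protocol article anticipates 30% quitting in the intervention hospitals and 20% under usual care. It then gives the model that decides the question, a logit GEE specified thus: "quitting is predicted by time frame (baseline versus intervention period), intervention group (Tobacco Tactics versus usual care), and the product of those two variables". Its stated reason is "to assure that these differences are not just due to differences between the hospitals". The inference rests on the product: "The statistical significance of the product will indicate that the difference between the Tobacco Tactics and the usual care comparison sites depends on" whether the intervention is in place.

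The Data analysis section sets the correlation structure: "the hospital unit will be treated as the cluster", and "The correlation matrix will be of the exchangeable form, assuming the same correlation among any pair of patients in the same hospital unit". It adds that "several strategies will be used to counter the effects of hospital differences on our finding". These strategies are patient-level covariates if patient types differ among hospitals, a propensity score if there are too many such differences, and the pre/post comparison itself.

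Table 4 includes hospital site in the demographics row of its control variables ("marital status, employment, hospital site"). The Design section says that the two sets of three hospitals are, as sets, "matched on hospital size and percentage of minority patients".

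**The concern.** The patients surveyed before and after implementation are different people, and nothing in the article fixes each hospital's share of its group's sample in either period. With one intercept per group, the mean model compares pooled quit rates. Stable differences between hospitals are sure to drop out of the product only when the mix within each group stays the same, or changes alike in both groups. Clustering by unit sets the weights and standard errors; it does not put hospital into the mean model.

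If a hospital with higher background quitting supplies relatively more of the post-implementation sample, and usual care has no matching change, the product is positive with no intervention effect. A shift the other way masks a real effect. The model would then not give the assurance for which it is proposed. The point concerns bias in the estimate, not the choice of cluster for the standard errors.

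**Working it through.** **Inputs from the Protocol article.** Rates 30% and 20%, alpha 0.05, 80% power, 2,350 smokers, 58 units (11/9/9 in Group 1, 12/8/9 in Group 2), about 25% lost to follow-up, exchangeable correlation within unit.

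**Inputs assumed.** Hospital quit rates, hospital shares by period, the unit correlation, and that Group 1 is the group that shifts. The article gives none of these.

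**1. The plan's own figures.** The target effect is ln(0.3/0.7) − ln(0.2/0.8) = 0.539. The unclustered two-sided two-proportion size is 294 per arm, 588 in total. Reaching 2,350 needs a design effect of 2,350/588 = 4.00. With 2,350/58 = 40.5 patients per unit, that implies an ICC of (4.00 − 1)/(40.5 − 1) = 0.076. With 25% lost it is 0.068. If only half the sample is post-period it is 0.052, and with both reductions 0.035. The ICC is not stated, so 2,350 can be neither reproduced nor refuted. These values only show which correlations are relevant below.

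**2. The mechanism by arithmetic, before any GEE weighting.** There is no intervention effect and hospital rates are constant at 15/20/25%. Shares move from 50/30/20% to 20/30/50%.
- Before: 0.5×0.15 + 0.3×0.20 + 0.2×0.25 = 18.5%.
- After: 0.2×0.15 + 0.3×0.20 + 0.5×0.25 = 21.5%.
- Odds ratio: (0.215/0.785)/(0.185/0.815) = 1.21.

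With rates of 10/20/30% the move is 17.0% to 23.0%, OR 1.46. With 15/20/25% and a milder shift (40/35/25% to 30/35/35%), it is 19.25% to 20.25%, OR 1.07.

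**3. How a one-sided shift could arise.** The article says nurse training may take two to six months, depending on how far a hospital can release staff, and places the primary outcome at the time staff deliver the intervention on their own. Assume equal monthly recruitment, a 12-month window, and training of 2, 4 and 6 months. The post windows are then 10, 8 and 6 months, so shares go from 33/33/33% to 42/33/25%. With rates of 25/20/15%, quitting moves from 20.0% to 20.8%, a log-OR of 0.05 (10% of 0.539). With 30/20/10% it moves to 21.7%, a log-OR of 0.10 (19%). Usual care has no corresponding process. The GEE would reduce both figures.

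**4. The planned exchangeable GEE, simulated with no intervention effect.** 1,762 followed patients (75% of 2,350) and the Table 3 unit counts. Entries are the spurious log-OR of the product.

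| Assumed Group 1 rates | Assumed shares, before to after | Working correlation about 0.02: two simulations | Unit variation raised |
|---|---|---|---|
| 25/20/15% | 25/33/42 to 42/33/25% | 0.077; 0.063 | 0.033 (correlation 0.04), 0.020 (0.07) |
| 25/20/15% | 20/30/50 to 50/30/20% | 0.136; 0.123 | 0.066, 0.047 |
| 28/20/12% | 20/30/50 to 50/30/20% | 0.180; 0.174 | 0.108 (0.05), 0.076 (0.07) |

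A further run at a correlation of about 0.06 gave 0.06 to 0.10 for the larger shift. Separate simulations with 2,350 patients and a shift from 50/30/20% to 20/30/50% agree. Rates of 15/20/25% gave OR 1.20, 1.13 and 1.08 at correlations of 0.004, 0.017 and 0.058. Rates of 10/20/30% gave 1.23, 1.19 and 1.10 at 0.019, 0.033 and 0.073.

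**5. Conditions under which it vanishes.** Constant mix: −0.004 in one simulation, OR 0.99 in another. Equal hospital rates with a shift: OR 1.00. Same rates and same shift in both groups: −0.01 to −0.02, with a simulation SE of 0.015.

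**6. With hospital indicators added.** In the 1,762-patient simulation the bias was −0.003 to 0.010, and in the 2,350-patient one the OR was 0.98 to 1.03. The SD of the estimate rose by at most about 4%.

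**7. False positives.** With 400 replicates, the larger shift gave about 8% (25/20/15%) and 12% (28/20/12%), against about 6% with indicators. The simulation SE is √(0.08×0.92/400) = 1.4 points at 8% and 1.2 at 6%, so only the 12% clearly stands apart.

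**The case against.** A reader might infer that every change in hospital mix passes in full into the product. The documents do not support that. Hospitals within a group must differ in quit rate, the shift must line up with those rates, and the other group must not shift likewise. The exchangeable correlation also gives weight to within-unit pre/post contrasts, which absorb part of the leak, and more of it as the correlation rises. At the correlations that 2,350 would imply if all the inflation were clustering, the bias is well below its value at 0.02. All of this stands.

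The scenarios are also constructed. The article reports no hospital quit rates and no enrolment shares by period. Group 1 discharge shares are 41/35/24% (19,800, 17,000 and 11,400 of 48,200), so a swing from 20/30/50% to 50/30/20% is severe. The minority percentages in Table 3 (70%, 4% and 27% in Group 1) show that the hospitals are unlike, but not that quit rates differ or recruitment drifts. This stands too, and limits what can be said about size.

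Finally, the omission may be only apparent. Table 4 lists hospital site as a control variable, Aim 2 says baseline quit rates will be taken into account whether or not hospitals differ, and a condensed article may leave the full covariate list to an analysis plan. This stands in part: one cannot conclude that hospital will be left out of the final analysis. But the article does write out the mean model and claims protection against hospital differences for it. The baseline-rate statement gives no method beyond the product. The covariate and propensity provisions are conditional and concern patient types. The model sentence and Table 4 still need reconciling.

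**Conclusion.** The concern holds in limited form. As written, the deciding model does not guarantee what it is offered to guarantee, because stable hospital differences can leak into the product when hospital mix shifts in one group only. Under sizeable assumed shifts the spurious log-OR is about 0.08 to 0.18 (15% to 33% of 0.539) at a working correlation near 0.02, and about 0.02 to 0.10 (4% to 19%) at 0.06 to 0.07. It is nil with a constant mix or equal hospital rates. These sizes rest wholly on assumed rates, shares and correlations. Nothing in the article shows that a shift will occur, and its direction cannot be predicted. The case for a change is that the stated model leaves a known route to bias open, the variable that closes it is already collected, and the cost is small.

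**What to change.** In the Aim 2 model, replace the two-level group main effect with indicators for the six hospitals, which absorb group, and keep period and the period-by-group product. The product then measures within-hospital change, as an odds ratio conditional on hospital. Use the same form for the other Aim 2 outcomes, and state that this is how hospital site in Table 4 enters the analysis. Report enrolment and follow-up counts by hospital and period, so that readers can see whether the mix moved.

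The cost is one sentence of analysis text, four more parameters and up to about 4% more variability in the estimate. No new data are needed. The change does not deal with hospital-level change over time when there are only six hospitals; that limitation remains and should be acknowledged separately.
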